### Aims and hypotheses

The goals are to assess levels of periodontal disease among a group of Aboriginal adults with CKD and to determine if comprehensive periodontal therapy might reduce progression of CKD, non-invasive measures of cardiovascular disease (CVD) or CKD/CVD-related death amongst people with CKD over 6 to 24 months. The specific aims and hypotheses are:Aim 1: To describe the extent and severity of periodontal disease in a group of Aboriginal adults with CKD.*Hypothesis: The extent and severity of periodontal disease in an Aboriginal population with CKD will be high compared with national-level indicators.*Aim 2: To examine the effects of a comprehensive periodontal intervention among an Aboriginal population with CKD.*Hypothesis: Exposure to a comprehensive periodontal intervention will reduce progression of CKD, non-invasive measures of CVD or CKD/CVD-related death amongst those with CKD.*

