### Inclusion criteria

Aboriginal people aged 18+ years who have lived in the study location for 2+ years, and who plan to live at their current location for the next 2 years, with CKD (i. on dialysis; ii. eGFR levels of <60 mls/min/1.73 m^2^ (CKD Stages 3 to 5); iii. ACR ≥30 mg/mmol irrespective of eGFR (CKD Stages 1 and 2); iv. diabetes plus albuminuria (ACR ≥ 3 mg/mmol) irrespective of eGFR), with at least 12 teeth at baseline and having moderate or severe periodontal disease will be invited to take part in the study. Periodontal disease will be assessed using the US Centers for Disease Control and Prevention and the American Academy of Periodontology definitions, whereby a case of moderate periodontitis is considered as the presence of either two sites between adjacent teeth with 4 mm + attachment loss or at least two such sites with 5 mm + pockets, and severe periodontitis as having at least two sites between adjacent teeth with 6 mm + attachment loss and at least one 5 mm + pocket [44].

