### Sample size

Based on a recent study of Australian Aboriginal adults with periodontal disease, it was estimated that a sample size of 472 would be necessary to detect a difference in cIMT of 0.026 mm (SD 0.09) [46] at the significance criterion of 0.05 and a power of 0.80. Allowing for 20 % attrition, 592 participants would be necessary at baseline, rounded to 600 for convenience.

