### Data analysis

Data analysis will use intention-to-treat and per-protocol approaches, with the effect on primary outcomes based on intention-to-treat analyses. Analyses will follow a general course of descriptive statistics such as distributions and measures of association. Simple cross-tabulations and more elaborate repeated-measures analyses will follow. In brief, the plan for the analysis of each aim is:*Aim 1: Extent and severity of periodontal disease compared with national-level counterparts:* Extent of periodontal disease will be defined by the number of periodontal sites in the mouth with a given pocket depth (PD) divided by the number of teeth in the mouth x 100. The National Survey of Adult Oral Health dataset will enable comparison with both general and Aboriginal population-level estimates [49]. General analysis will comprise Chi-square and Student’s t-test within the study sample and non-overlapping 95 % confidence intervals when comparing with population estimates.*Aim 2: Changes in cIMT, measures of renal function and CKD/CVD-related death:* The primary analysis will compare changes in cIMT and 95 % confidence intervals. Secondary analyses will examine each outcome variable using separate mixed models, to allow inclusion of all participants without having to impute data. We will use generalised linear mixed models for non-continuous outcomes. Models will include treatment group as a fixed effect. Analyses will be conducted to identify subgroups that modify the response to the intervention (eg. active/passive smoking, socio-economic status). Model assumptions will be checked and appropriate adjustments made. We will conduct sensitivity analyses to assess uncertainty in key parameters. Death and cardiovascular events, both binary outcomes, will be analysed using the chi-square test with frequencies and percentages per treatment arm and odds-ratios or other measures of treatment effect reported along with summary measures. The Greenhouse-Geisser correction for the F-test will be used to adjust the degrees of freedom for deviation from sphericity. Logarithmic transformation of the data will be performed where appropriate. A post hoc correlation analysis by the Spearman rank-correlation method will be performed to evaluate the relationship between the changes in renal function and cIMT from baseline to 6, 12 and 24 months following periodontal therapy. The same will also be done for measures of periodontal health and cIMT. Effect sizes will be calculated by dividing the mean of change scores by the pooled estimate of the standard deviation. Effect measures will also be presented through calculation of number-needed-to-treat and its associated 95 % confidence interval. The statistically significant level will be at α < 0.05.

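### Aim 1 judges differences from population estimates by non-overlap of two 95% confidence intervals, a rule stricter than the plan's 0.05 level by an amount the documents do not fix (minor)

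*Protocol article*

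**What the plan says.** The protocol article (Aims and hypotheses) attaches a hypothesis to Aim 1: "The extent and severity of periodontal disease in an Aboriginal population with CKD will be high compared with national-level indicators".

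The Data analysis section names the comparator: "The National Survey of Adult Oral Health dataset will enable comparison with both general and Aboriginal population-level estimates". It then separates two kinds of comparison. Chi-square and t-tests are for comparisons within the study sample. For the external comparison the criterion is "non-overlapping 95 % confidence intervals when comparing with population estimates". No other test, and no interval for the difference, is given for that comparison.

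The section closes with one level for the whole analysis: "The statistically significant level will be at α < 0.05". No exception is made for Aim 1.

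**The concern.** Checking whether two separate 95% intervals overlap is not the same as testing their difference at 5%. Separation of the intervals adds the two standard errors, while the standard error of a difference adds their squares and takes the root. The sum is always larger than the root unless one standard error is zero. A reader who takes the 0.05 at face value would therefore be misled about the level at which Aim 1 is judged.

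Two consequences follow. First, a moderate difference can be significant on a direct test and still fail the rule. Second, the plan makes two external comparisons, with the general and with the Aboriginal population. If the survey's standard errors differ between them, one rule works at two different unstated levels, and a contrast such as higher than one population but not the other could partly reflect the rule. The rule also produces no estimated difference with an interval, which is what a reader needs to judge how high the burden is.

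**Working it through.** **Inputs from the protocol article**
- Decision rule and significance level: Data analysis. The 0.05 is taken as two-sided, since sidedness is not stated.
- Study sample at baseline: 600, from Sample size ("Allowing for 20 % attrition, 592 participants would be necessary at baseline, rounded to 600 for convenience").

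**Assumptions**
- The study and survey estimates are independent and approximately normal.
- The ratio of standard errors, r, is assumed. The survey's sample size and standard errors are not in the documents. Results are the same for r and 1/r.

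**Step 1. The two thresholds for a difference d**
- Non-overlap of two 95% intervals: |d| > 1.96(SE1 + SE2)
- Two-sided 5% test: |d| > 1.96√(SE1² + SE2²)

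**Step 2. The critical value that the rule implies**

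Dividing the first threshold by √(SE1² + SE2²) gives z = 1.96(1 + r)/√(1 + r²). The level is 2[1 − Φ(z)]. The plan's 0.05 is recovered only in the limit where one standard error is zero: r = 0 gives z = 1.96.

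**Step 3. Power**

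A difference for which the direct test has 80% power lies 1.960 + 0.842 = 2.802 standard errors from zero. Under the rule its power is Φ(2.802 − z).

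| r (assumed) | z | Actual level | Power (direct test: 80%) |
|---|---|---|---|
| 1 | 1.96 × 2/√2 = 2.772 | 0.0056 | 51% |
| 2 | 1.96 × 3/√5 = 2.630 | 0.0085 | 57% |
| 3 | 1.96 × 4/√10 = 2.479 | 0.013 | 63% |
| 10 | 1.96 × 11/√101 = 2.145 | 0.032 | 74% |

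A simulation with 2 million draws gave a level of 0.0055 at r = 1, which agrees.

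**Step 4. The same in terms of survey size**

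Take 600 participants, equal standard deviations and an assumed effective survey size m, so that r = √(600/m).

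| m (assumed) | Actual level | Power (direct test: 80%) |
|---|---|---|
| 200 | 0.007 | 55% |
| 600 | 0.006 | 51% |
| 2,000 | 0.008 | 56% |
| 5,000 | 0.013 | 62% |
| 10,000 | 0.018 | 67% |
| 50,000 | 0.031 | 74% |

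If, purely for illustration, the effective size were 200 for the Aboriginal estimate and 5,000 for the general one, the same rule would run at 0.007 in one comparison and 0.013 in the other.

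**Step 5. Size on the outcome scale, in the worst case (equal standard errors, 600 in each group)**
- Continuous measure: SE = SD/√600 = 0.0408 SD. Non-overlap needs 1.96 × 2 × 0.0408 = 0.16 SD; the direct test needs 1.96 × √2 × 0.0408 = 0.11 SD.
- Proportion near 50%: SE = 0.5/√600 = 0.0204. Non-overlap needs 8.0 percentage points; the direct test needs 5.7.

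The rule thus costs about 0.05 SD, or 2.3 percentage points, in the size of difference needed.

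**The case against.** The strongest reply is that little hangs on this. Aim 1 sets out to describe disease, in a non-randomised comparison with an external survey. The primary outcome is change in cIMT, which has its own analysis, so neither the sample size nor the treatment conclusion is affected. The rule errs on the cautious side and makes a false claim of difference less likely, not more. All of this stands, and it is why the point is minor.

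A reader might go further and infer that the rule is far stricter than 0.05. The documents do not establish that. It holds when the standard errors are similar, but the level returns towards 0.05 as one of them becomes negligible, and the survey's precision is not given.

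A reader might also infer that real differences will be missed. That is not shown either. The power figures concern a difference placed exactly where a direct test has 80% power. The documents point towards larger ones, because eligibility is limited to people "with at least 12 teeth at baseline and having moderate or severe periodontal disease will be invited to take part in the study". Nor does the plan say that overlapping intervals will be taken as proof of no difference; it only makes non-overlap the criterion.

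Survey weighting and age or sex standardisation are details that a condensed article may leave to the full plan, so their absence is no fault here. What the reply does not remove is that the article names a specific rule, and that rule does not have the level stated in the same section. This is a wrong statement, not an omitted detail. It is true that the closing 0.05 follows the Aim 2 methods, so applying it to Aim 1 is an inference, but it is the only level given and it is stated without restriction.

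**Conclusion.** Wrong as written, and minor. Non-overlap of two 95% intervals is stricter than a 0.05 test of the difference whenever the survey estimate, like the study estimate, has sampling error. The direction is certain; the size rests on an assumed ratio of standard errors. For ratios of 1 to 10 the level is 0.0056 to 0.032, and 80% power under a direct test becomes 51% to 74%. The level can also differ between the general and the Aboriginal comparison.

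The error is conservative, touches only the descriptive Aim 1 comparison, and would not hide a large difference. It has no bearing on the randomised cIMT comparison.

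A heavier problem for the same comparison is separate. Because enrolment requires moderate or severe periodontal disease, a high result against the population is partly built in, and a correct test does not change that.

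**What to change.** In the Data analysis section, replace the non-overlap rule for Aim 1 with the estimated difference (or ratio) between the study sample and each survey estimate. Give it its own 95% confidence interval and a test. For a difference, base both on SE = √(SE1² + SE2²), taking the survey's design-based standard error as SE2; for a ratio, work in the same way on the log scale.

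The cost is one sentence. No new data are needed, since the article says that the survey dataset will be used. The selection of participants on periodontal disease has to be dealt with separately, at least by stating it as a limit on what the Aim 1 comparison can show.

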**Methods:**

The study will be a randomised controlled trial. All participants will receive the periodontal intervention benefits, with the delayed intervention group receiving periodontal treatment 24 months following baseline. Inclusion criteria include being an Aboriginal Australian, having CKD (a. on dialysis; b. eGFR levels of <60 mls/min/1.73 m^2^ (CKD Stages 3 to 5); c. ACR ≥30 mg/mmol irrespective of eGFR (CKD Stages 1 and 2); d. diabetes plus albuminuria (ACR ≥ 3 mg/mmol) irrespective of eGFR), having moderate or severe periodontal disease, having at least 12 teeth, and living in Central Australia for the 2-year study duration. The intervention involves intensive removal of dental plaque biofilms by scaling, root-planing and removal of teeth that cannot be saved. The intervention will occur in three visits; baseline, 3-month and 6-month follow-up. The primary outcome will be changes in carotid intima-media thickness (cIMT). Secondary outcomes will include progression of CKD or death as a consequence of CKD/cardiovascular disease. Progression of CKD will be defined by time to the development of the first of: (1) new development of macroalbuminuria; (2) 30 % loss of baseline eGFR; (3) progression to end stage kidney disease defined by eGFR <15 mLs/min/1.73 m^2^; (4) progression to end stage kidney disease defined by commencement of renal replacement therapy. A sample size of 472 is necessary to detect a difference in cIMT of 0.026 mm (SD 0.09) at the significance criterion of 0.05 and a power of 0.80. Allowing for 20 % attrition, 592 participants are necessary at baseline, rounded to 600 for convenience.

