### Follow up

Participants will be followed for 24 months after randomisation. Because this is a pragmatic study evaluating the delivery of periodontal care, rather than therapeutic agents, an open design is necessary. Appropriate care will be taken to ensure standardised, and where feasible, blinded outcome evaluation—“PROBE” design [45]. During follow-up, all study participants will attend clinic visits at 6 months, 12 months and at 24 months.

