### Measures

*Primary outcome:* The primary outcome will be change in cIMT over 24 months from randomization.

*Secondary outcomes;* will include progression of CKD, death as a consequence of CKD/CVD, periodontal status, endothelial function, arterial stiffness, measures of inflammation and infection, CVD risk factors (blood pressure, total cholesterol, HDL-cholesterol, HbA1c), CV events (myocardial infarction, coronary revascularisation procedures, ischaemic cerebrovascular disease, peripheral vascular disease, ischaemic stroke) and oral health-related quality of life. Progression of CKD will include time to the development of the first of: (1) new development of macroalbuminuria (defined as ACR ≥30 mg/mmol); (2) 30 % loss of baseline eGFR (defined as a reduction of eGFR of 30 % or more from baseline and eGFR of less than 60mLs/min/1.73 m2); (3) progression to ESKD defined by eGFR <15 mLs/min; (4) progression to ESKD defined by commencement of renal replacement therapy.

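### CKD progression is defined as time to first event, but the analysis section puts it under mixed models and names no time-to-event method

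*Protocol article*

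**What the plan says.** The endpoint is a time in both places where it is defined. The Abstract (Methods) has "Progression of CKD will be defined by time to the development of the first of", and the Measures section has "Progression of CKD will include time to the development of the first of". In each the list is macroalbuminuria, a 30% fall in eGFR, ESKD by eGFR, or ESKD by start of renal replacement therapy.

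The Data analysis section (Aim 2) then says: "Secondary analyses will examine each outcome variable using separate mixed models, to allow inclusion of all participants without having to impute data". It adds: "We will use generalised linear mixed models for non-continuous outcomes". Two outcomes are treated separately: "Death and cardiovascular events, both binary outcomes, will be analysed using the chi-square test", with odds ratios or other effect measures. The section also promises a number needed to treat with its 95% confidence interval. No survival curve, hazard model, log-rank test or censoring rule appears in the article.

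On follow-up: "Participants will be followed for 24 months after randomisation", and "all study participants will attend clinic visits at 6 months, 12 months and at 24 months".

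On death, Measures lists the outcomes side by side: secondary outcomes "will include progression of CKD, death as a consequence of CKD/CVD, periodontal status" and so on. The Abstract instead joins CKD progression and CKD/CVD death with the word or.

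**The concern.** A time to first event carries two pieces of information: whether the event happened and when, or how long the person was observed without it. A mixed model for repeated measurements, or a generalised linear mixed model for binary status at visits, does not use the second piece unless it is set up to do so. A first event also cannot be undone, so modelling status at each visit answers a different question from the one the definition asks. An analyst following the article could not tell which effect measure for CKD progression is intended, nor how someone lost or dead before progressing enters the analysis.

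Death and cardiovascular events raise a smaller question. They carry no time-to definition, so nothing is contradicted. But a chi-square test needs a yes or no for everyone. If some participants are lost, a rule must supply that answer, and the rule affects the reported risks and any number needed to treat derived from them.

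These outcomes are secondary, but the Discussion rests its practice message on slower CKD progression and fewer CVD events.

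**Working it through.** **1. Endpoint against method**

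| Outcome | Defined as | Stated analysis | Match |
|---|---|---|---|
| CKD progression | Time to the first of four events (Abstract, Measures) | Mixed model or GLMM, as one of the secondary outcomes | No |
| CKD/CVD death | Event, no time stated (Measures) | Chi-square; the article calls it binary | Consistent, if 24-month status is known |
| CV events | Events, no time stated (Measures) | Chi-square; the article calls them binary | Consistent, if 24-month status is known |

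CKD progression is not named in the mixed-model sentence. It falls there because that sentence covers each outcome variable and the chi-square sentence covers only the other two.

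**2. Inputs for the chi-square point**

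The article gives no event rate, event count or power for these outcomes, so it has no figure to reproduce. From the article: 600 randomised, taken as 300 per arm, and 24 months of follow-up. It also gives 20% attrition, but in the cIMT sample-size section. Assumed: event risks of 5% to 40%, loss by arm, constant hazards, and loss independent of outcome.

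Let r be the true 24-month risk and l the loss. With time in units of 24 months, h = −ln(1−r) and g = −ln(1−l).

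- Lost counted as event-free: observed risk p = h/(h+g) × (1 − e^−(h+g)).
- Lost without an event dropped, earlier events kept: p / (p + e^−(h+g)).

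**3. Equal loss of 20%, true risk 30%**

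h = 0.3567, g = 0.2231, h+g = 0.5798, e^−0.5798 = 0.560.

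- Event-free rule: 0.6152 × 0.440 = 0.2707, so 27.1%.
- Dropping rule: 0.2707 / (0.2707 + 0.560) = 0.3258, so 32.6%.

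Both arms are misstated alike, so the test keeps its size. In simulation (300 per arm, 4,000 runs, 20% loss in each arm, no effect), two chi-square versions (lost as event-free; lost dropped) and the log-rank test all rejected about 5%. At a hazard ratio of 0.7 and a 40% control risk, power was 66%, 66% and 68% respectively.

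**4. Unequal loss of 15% versus 25%, no true effect, lost counted as event-free**

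With d = p1 − p2 and s = √(2p̄(1−p̄)/300), where p̄ is the mean of p1 and p2, the rejection rate is Φ(−1.96 + d/s) + Φ(−1.96 − d/s). At 30% risk: d = 0.2782 − 0.2629 = 0.0153, s = 0.0363, d/s = 0.42, giving 0.062 + 0.009 = 0.071.

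| True risk, both arms | Observed, 15% loss | Observed, 25% loss | Spurious difference (points) | Type I error |
|---|---|---|---|---|
| 5% | 4.6% | 4.4% | 0.3 | 5.3% |
| 10% | 9.2% | 8.7% | 0.5 | 5.6% |
| 20% | 18.5% | 17.5% | 1.0 | 6.3% |
| 30% | 27.8% | 26.3% | 1.5 | 7.1% |
| 40% | 37.2% | 35.2% | 2.0 | 8.0% |

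**5. A larger assumed imbalance**

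With 30% loss in control and 10% in intervention, simulated type I error was 10.5% (lost as event-free), 10.1% (lost dropped) and 5.5% (log-rank) at a 20% risk, and 17.5%, 11.7% and 5.5% at a 40% risk. Log-rank holds because the simulated loss was non-informative. It would not correct loss related to prognosis.

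**The case against.** The strongest reply is that a generalised linear mixed model can be a survival model. ACR and eGFR are seen only at 6, 12 and 24 months, and a discrete-time complementary log-log model belongs to the generalised linear family. The mixed models were also chosen so that participants with incomplete data stay in, so incomplete follow-up was considered. And the section is written as a summary, with an analysis plan that may add detail.

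Much of this stands. A reader might infer that none of the named methods could handle follow-up time; that is too strong. What remains is that the article does not say that such a model is meant. It names a method family that, taken plainly, does not fit the endpoint. This is a stated method that does not match, rather than detail left out. By contrast, detailed censoring and competing-risk rules may properly sit in an analysis plan, and their absence alone is no fault.

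Three other inferences are tempting and not supported:

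- *That the chi-square test is wrong for death and CV events.* The article defines these as binary over a fixed period. The test is sound with complete ascertainment, and it keeps its size under equal loss independent of outcome. Nor is every way of handling loss biased: for non-fatal events under independent loss, restricting to participants followed to 24 months recovers the true 30%.
- *That participants who die before progressing are counted as not progressing.* The article does not say so. The Abstract can be read as a composite in which CKD/CVD deaths are events.
- *That 20% of event information will be lost.* That figure belongs to cIMT, which needs an attended scan. Vital status or dialysis start may be better known, and the article lists extensive tracing. It gives no loss by arm; imbalance is plausible in an open trial with delayed control treatment, but it is an assumption.

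**Conclusion.** The mismatch is real for CKD progression: a time-to-first-event definition in two places, an analysis sentence that puts it under mixed models, and no time-to-event method named. This rests on the text alone and needs no assumed rates. The unclear role of CKD/CVD death adds to it: if such death is part of the composite, only death from other causes competes with progression; if it is separate, all deaths before progression compete.

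The chi-square point is secondary and conditional. Its effect on type I error ranges from negligible (5.3% at a 5% risk) to modest (8.0% at 40%) under 15% versus 25% loss with lost counted as event-free, and it vanishes under equal independent loss. The arm-level risks are still understated under that counting rule even when loss is equal. All these figures depend on assumed event risks and losses.

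The primary cIMT analysis and the sample size do not depend on any of this. It should be corrected, but it does not threaten the trial's main result.

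**What to change.** 1. State that CKD progression is analysed as time from randomisation to the first component event, censored at last contact. Because ACR and eGFR are observed only at 6, 12 and 24 months, use a discrete-time complementary log-log model, or an interval-censored or Cox equivalent.
2. State a cause-specific treatment of death before progression, and reconcile the Abstract with Measures on whether CKD/CVD death is a component or a separate outcome.
3. As a cheap further improvement, report CKD/CVD death and first CV event by cumulative incidence with a cause-specific hazard ratio. Take the 24-month risk difference, its 95% confidence interval and the number needed to treat from the cumulative incidence. If chi-square is kept, say how 24-month status is ascertained and how lost participants are handled.

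The cost is analysis wording. It needs event dates and last-contact dates, which a time-to-event definition already implies; it needs no extra visits and no change in sample size.
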